### Eligibility criteria

Eligibility criteria consists of ≥16 years of age, singleton cephalic (head down) pregnancy, ≥ 37 weeks gestation, spontaneous or induced labour, no serious concurrent medical conditions (pre-eclampsia, coagulopathy, diabetes other than diet controlled), cognitively capable of providing consent, able to read and understand instructions written in English. Upon admission to the birth suite randomisation will occur when the participant’s self-assessment of labour pain ≥60 mm (Visual Analogue Scale [VAS] 0-100 mm, 0 = no pain 100 = worst conceivable pain), and requesting pain relief.

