### Outcomes

The primary outcome for the trial is the mean difference in VAS scores of labour pain between intervention and control groups at 30 min following the administration of the injections. Secondary outcomes include the number of women experiencing an at least 30% or 50% reduction in pain following the injections. This is the measure of analgesic effectiveness recommended in the Cochrane Review of water injections for back pain in labour [29]. Other secondary outcomes are detailed in Table 1.

**Table 1 Tab1:** Schedule of enrolment, interventions and assessments

		Study period					
			Post-allocation				Close-out
	Enrolment	Allocation	*Time periods after injection*			*1–14 days post birth*	*From perinatal database*
TIMEPOINT**			*30 min*	*60 min*	*90 min*		

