### Sample size

We have calculated the sample size based on the recommended minimal clinically significant reduction in VAS scores: 10 mm difference on a 100 mm VAS score between intervention and placebo [30]. To demonstrate a 10 mm reduction (SD 20 mm) in VAS scores with 80% power and 0.05 significance (two-sided) would require 64 participants per group. Based on previous studies [15] we estimate an attrition of 20% due primarily to women giving birth or requesting epidural analgesia prior to the measurement of the primary outcome. The total sample size required would be 154 participants, 77 per trial group.

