### Data analysis

All women who underwent randomisation and for whom primary outcome data is available will be analysed in their allocated treatment groups regardless of the intervention received (i.e. intention to treat). Randomisation should ensure that any baseline differences between groups occur by chance. To control for cluster effect repeated measurement, a linear mixed-model analysis will be conducted to investigate the difference in mean VAS score pre and post intervention. Missing VAS data will be addressed through imputation (last observation carried forward) A sensitivity analysis will be conducted following imputation to assess any effect on findings. Clinical data will be analysed on an available case basis with numbers of participants with missing data presented in the results tables. Categorical data will be analysed with chi-squared tests and non-repeated continuous variables will be analysed with t-tests if normally distributed or Mann-Whitney U test if non-normally distributed. Additional multivariable analysis will be employed if baseline differences are noted between the two groups. Treatment effects will be presented as mean difference or relative risks with 95% confidence intervals. All study outcomes will be analysed using a two-sided *P* value of < 0.05 to indicate statistical significance. We do not plan to undertake any subgroup analysis or interim analysis.

For the postnatal survey data descriptive statistics will be calculated for all variables, including mean, median, standard deviation, range, and percentages as appropriate. Free text responses will be analysed thematically.

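### Adjustment is made to depend on observed baseline imbalance, and the wording of the primary VAS model does not secure the precision that pre-injection VAS could give

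*Protocol article*

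**What the plan says.** All quotes are from the protocol article.

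- **Data analysis, chance differences:** "Randomisation should ensure that any baseline differences between groups occur by chance".
- **Data analysis, trigger:** "Additional multivariable analysis will be employed if baseline differences are noted between the two groups". No criterion for noting a difference and no covariates are given. Nothing says whether the adjusted or the unadjusted result takes precedence.
- **Data analysis, VAS model:** "a linear mixed-model analysis will be conducted to investigate the difference in mean VAS score pre and post intervention". How the pre-injection value enters the model is not stated.
- **Outcomes:** the primary outcome is "the mean difference in VAS scores of labour pain between intervention and control groups at 30 min" after the injections, which is a between-group contrast at one time point.
- **Sample size:** the target is a "10 mm difference on a 100 mm VAS score between intervention and placebo", sized as a plain two-group comparison.
- **Eligibility criteria:** "randomisation will occur when the participant’s self-assessment of labour pain ≥60 mm", so baseline VAS can only lie between 60 and 100 mm.
- **Table 1:** labour-pain VAS before the injections and cervical dilation are both recorded at allocation.

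**The concern.** There are two linked problems.

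First, the trigger is driven by the data. If baseline differences are chance differences, as the section itself says, then seeing one is no reason to adjust. The reason to adjust is that a covariate predicts the outcome, and that can be judged before any data are seen. Under the stated rule a strongly prognostic but balanced covariate is left out, and an irrelevant but imbalanced one is brought in. When the trigger fires there are two results, with no stated order between them.

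Second, the obvious prognostic covariate for 30-minute VAS is pre-injection VAS. The planned model includes it, but the wording is compatible with several models of quite different precision. The trial is sized at 80% power with little to spare, so the choice between them matters.

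**Working it through.** **Inputs.** Difference 10 mm, SD 20 mm, two-sided 0.05, 80% power, 64 per arm (Sample size). The correlation r between pre-injection and 30-minute VAS is not in the document, so 0.3, 0.5 and 0.7 are assumed.

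**1. The plan's own figure.** n per arm = 2 × (1.960 + 0.842)² × 20² / 10² = 62.8, so 63 by the normal approximation. The t-test solution is 63.77, so 64. This reproduces the stated 64 per group and confirms that the sizing is for an unadjusted comparison.

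**2. Power at 64 per arm.** Power = Φ(10 / (SD × √(2/64)) − 1.96), with the SD that belongs to each analysis:

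- unadjusted 30-minute comparison: SD = 20
- change score, which is what the group-by-time contrast in a mixed model with unconstrained baseline means estimates: SD = 20 × √(2(1 − r)), taking an SD of 20 mm at both times
- fixed adjustment for baseline, as a covariate or with a common baseline mean: SD = 20 × √(1 − r²)

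| r | Unadjusted | Change score (SD) | Always adjusted (SD) |
|---|---|---|---|
| 0.3 | 80.7% | 66.7% (23.66) | 84.3% (19.08) |
| 0.5 | 80.7% | 80.7% (20.00) | 90.4% (17.32) |
| 0.7 | 80.7% | 95.5% (15.49) | 97.7% (14.28) |

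With equal SDs, the change score beats the unadjusted comparison only when 2(1 − r) < 1, that is r > 0.5. Fixed adjustment is at least as precise as either at every r.

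**3. How far the 67% depends on equal SDs.** The entry threshold probably makes the baseline SD smaller than 20 mm. If baseline VAS were uniform on 60 to 100 mm (an assumption), its SD would be 40/√12 = 11.5 mm. The change-score variance is then 400 + 133.3 − 2 × r × 20 × 11.55:

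- r = 0.3: 394.8, SD 19.87, power 81%
- r = 0.5: 302.4, SD 17.39, power 90%
- r = 0.7: 210.0, SD 14.49, power 97%

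The change-score penalty shrinks, and at r = 0.3 the gain from fixed adjustment over either alternative is about 3 to 4 points. The ordering does not change.

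**4. What the trigger does on its own.** Simulation of 40,000 trials at 64 per arm: a plain 30-minute t-test, replaced by the baseline-adjusted analysis only if baseline VAS differs at p < 0.05.

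| r | Power, triggered | Power, always adjusted | Type I error, triggered |
|---|---|---|---|
| 0.3 | 80.5% | 83.2% | 4.8% |
| 0.5 | 81.1% | 90.0% | 4.3% |
| 0.7 | 82.1% | 97.6% | 3.5% |

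A trigger recovers little of the available gain, and its type I error falls below nominal. If the better of the two results were taken whenever the trigger fired, type I error would be about 5.0% to 5.1%. Only free choice in every trial raises it, to 6.4%, 7.3% and 8.2%. This simulation describes a plain 30-minute comparison with a trigger, not the planned mixed model, so it shows how such a rule behaves and not the loss in this trial.

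**The case against.** **Baseline VAS is already used.** A reader might infer that the plan throws away the information in pre-injection VAS unless an imbalance appears. The document does not support that: the mixed model takes in pre- and post-injection VAS whatever the trigger does. This stands, and it means the triggered-versus-always power gaps cannot be quoted as losses of this plan. It does not settle the matter, because the model as worded could be read as a change-score analysis, an unadjusted 30-minute contrast or a baseline-adjusted one.

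**Type I error.** A reader might also infer that the rule inflates false positives. The calculations show otherwise: replacing one result by the other is conservative, and picking the better one only when triggered stays near 5%. Randomisation and blinding also says that the analysis is done blind to group, which limits selection by direction of effect.

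**Frequency of the trigger.** With 10 independent baseline variables each tested at 0.05, at least one would differ in 1 − 0.95¹⁰ = 40% of trials. The document gives neither that count nor that test, so the figure is only an illustration.

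**Supplementary status.** The sentence speaks of an additional analysis and follows the tests for categorical and non-repeated outcomes. It most naturally means a supplement, perhaps not to the primary model at all. That is a fair reading, but the text does not say so.

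**Left to the SAP.** A covariate list, a criterion and details of the model can wait for the SAP. The trigger is different: it is a rule already stated, and a SAP would have to reverse it.

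**Conclusion.** The concern holds in a limited form. The protocol article states a rule under which observed imbalance decides whether adjustment happens. That conflicts with its own remark that such differences are due to chance, and it leaves the standing of the adjusted result open. Separately, the primary model uses pre-injection VAS but is described in a way that does not tie it to the 30-minute between-group difference with baseline adjusted.

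At 64 per arm, fixed adjustment would give about 84% to 98% power over r = 0.3 to 0.7, against about 81% unadjusted. A change-score analysis ranges from about 67% to 95% if the SD is 20 mm at both times, and is less poor at low r if the entry threshold narrows the baseline spread. The threshold also makes the lower values of r more likely, so the realistic gain over an unadjusted comparison lies towards the lower end. All these figures rest on an assumed r. The main harm is lost precision. The trial is not invalidated, and inflated type I error is not shown.

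**What to change.** In the Data analysis section:

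1. Delete the sentence that makes multivariable analysis depend on noted baseline differences.
2. State that the primary estimate is the between-group difference in VAS at 30 minutes, from a model that always adjusts for pre-injection VAS, either as a covariate or through a common baseline mean in the mixed model.
3. Label any further adjusted model as a sensitivity analysis, name its covariates in advance, and run it whatever the observed balance.

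The cost is analysis wording only. Pre-injection VAS is already collected at allocation, and no extra participants or data items are needed.

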### Economic analysis

A cost-effectiveness analysis will be undertaken to compare costs and outcomes of between intervention and placebo groups from the perspective of the health system. The approach to identification, measurement and valuing resource use will follow a similar approach to that which we have used in previous studies [15]. Information about resource use and costs will be collected at the research site. In the case of the intervention, resources to be identified and measured will include those associated with the establishment of the intervention (staff training, development of educational resources and credentialing) and staff time required for administration. Costs will be allocated to the relevant resource items using appropriate values. For example, staff time will be costed using hourly award rates plus on-costs; and the costs of length of stay and complications from admission to discharge of hospital will be estimated using appropriate Diagnostic Related Groups. The outcome for the economic evaluation is VAS pain score difference between two groups. The incremental cost-effectiveness ratio will be calculated and the cost-effectiveness acceptability curve will be graphed to summarise the uncertainty of cost-effectiveness according to different willingness to pay.

### Monitoring and reporting of risks

Standard Operational Procedures (SOPs) will be developed for risk management and reporting based on those used in previous clinical trials [15]. The SOPs will detail role responsibilities and processes for risk reporting and be reviewed and approved by a Data Safety Monitoring Board (DSMB) and trial Steering Committee. The DSMB members consist of an Obstetrician, midwife, statistician, and a consumer representative and provide independent oversight of the trial. The Steering Committee will consist of the Chief Investigators and Trial Manager and convene every 2 weeks. Each SOP will define and stratify any potential risk according to the University of Queensland Risk Level Calculator, which assesses the ‘likelihood’ versus the ‘consequences’ of risk and thereby assigns ratings from 1 = low to 5 = very high. The SOPs will also outline the standardised response and reporting procedure per risk level. Emergency code breaks for trial allocation will be available 24/7 if required. All adverse events will be reported and actioned immediately. The DSMB will manage the Risk Register, and recommend necessary modifications or termination of the trial. The DSMB will meet quarterly, or in response to serious adverse events and may undertake audits of trial conduct. Code breaking (unblinding) is possible in the event of a serious unexpected adverse event that requires identification of the allocated intervention to progress treatment. A sealed envelope containing the allocation will be held onsite in a secure location and accessible 24 h a day. Annual reports on trial progress will be provided to the Human Research Ethics Committee (HREC). The HREC will also be notified of any serious adverse events.

### Dissemination of findings

The results will be reported in conferences or peer-reviewed journals. The results will also be shared with participants, healthcare professionals and the public through lectures or science handbooks.

## Discussion

The provision of effective pain relief is a fundamental aspect of respectful, safe care during labour and birth [33]. Ideally, pharmacological analgesic options should support, rather than limit, women’s choices and plans to manage the pain of labour and be free of side effects that may negatively contribute to the experience and outcomes of labour. Currently none of the commonly available pharmacological options achieves this. What is needed is an analgesic option that is simple to administer, effective in reducing contraction pain, largely free of side effects and compatible with non-pharmacological techniques. The use of sterile water injections has the potential to fulfil this need. The technical simplicity of sterile water injections makes it suitable for use in all maternity care settings and by many levels of health care providers.

Our study will be the first placebo-controlled randomised trial to assess the use for sterile water injections to relieve the abdominal contraction pain of labour. The study design has the methodological strength to provide high level evidence efficacy and safety. The trial will also initiate the use of a vapocoolant spray to mitigate the pain associated with the administration of water injections and assess the impact of this approach on the acceptability of the procedure. The postnatal survey will assess women’s satisfaction with the allocated treatment and likelihood to reuse the same method in subsequent pregnancies. This experience of using water injections for abdominal labour pain will be further explored in proposed qualitative studies. The economic analysis will assess patterns and levels of resource utilisation associated with each participant across the two arms of the study. The combination of data and analysis will assist in contextualising findings from the RCT and enhance the understanding of the potential role of water injections as a labour pain analgesic.

The successful completion of our trial will see a new use for one of the most widely available medical preparations as an analgesic, improved choice for women and more efficient use of health resources.

## Trial status

Trial protocol version and date: Version 3 22 November 2021

Recruitment will commence 25th April 2022

Recruitment to be completed by 31st May 2023

## Data Availability

Access to the full trial protocol and data from this study will be confidential until the trial is completed and the database is closed at the end of the study. Following final publications the protocol and database will be open to other researchers upon request in line with National Health and Medical Research Council policy.

## Abbreviations

GP: General Practitioner
MGP: Midwifery Group Practice
VAS: Visual analogue scale
SOP: Standard Operational Procedure
DSMB: Data Safety Monitoring Board
GCP: Good Clinical Practice
